##### Monitoring of potential adverse events

After enrolment, each infant is visited by the enrolment team at hospital or home 1 day and 3 days after supplementation to ascertain adverse events. Newborns with adverse events are referred/escorted to the nearest health facility for management.

##### Follow up during infancy

Each enrolled infant is allocated to a home visit worker (contiguous study areas are allocated to FWs in advance) for further follow up visits till 12 months of age. All infants are contacted when aged 1, 3, 6 and 12 months by the home visit worker to document vital status, hospitalization, immunization, and information on feeding practices. Verbal autopsies are conducted to ascertain causes of deaths reported. Whenever hospital records are available these are photocopied and attached to the form. A hospitalization is defined as either an inpatient admission (where an infant receives an inpatient slip with a registration number and is allotted a bed) or a stay of ≥ 6 hours duration in the hospital including the emergency services, diarrhoea management room or any paediatric wards of the institution.

##### Blood samples

Blood specimens are being obtained from a subsample of infants at 2 weeks and mother infant pairs at 3 months for serum retinol, retinol binding protein concentrations and C- reactive proteins. Specimens will be collected over one calendar year and during one week every month. The study areas have been divided into four quadrants. Every month a blood specimen is requested from 60 randomly selected infants aged 2 weeks (up to +6 days) and 60 mother-infant pairs (infant aged 3 months up to +6 days) residing in one quadrant.

##### Data management

All data are captured electronically in net books. The data management centre is set up in the field office rented in the field sites. Range and logical checks are incorporated and cleaned data are sent to WHO every month.

#### Tanzania

##### Study setting

The study is being conducted in both urban and rural areas in Tanzania. In Dar es Salaam, the study is based in urban and semi-urban health facilities and their respective catchment areas. In Morogoro region, the study is carried out in Ifakara town and surrounding rural Kilombero, Ulanga and Kilosa districts nested within a demographic and health surveillance system. There are approximately 2.5 million people living in Dar es Salaam and 400,000 in Ifakara and surrounding areas. The 2004-05 Tanzania Demographic and Health Survey [27] estimated the infant mortality rate at 73 per 1000 live births in urban areas and 85 per 1000 live births in rural areas. The prevalence of Vitamin A deficiency for infants at age 6 months was reported to range from 26% to 41%.

##### Identification of newborns

Newborns are identified as part of a pregnancy and birth surveillance system or when an infant is born in selected labour wards in the study areas. Women recruited during pregnancy, either during routine antenatal care or through regular household visits conducted as part of the demographic and health surveillance system, are consented and followed closely during pregnancy. Information about household demographics, nutritional status, and pregnancy complications are collected during this time. For women recruited at labour wards, the same information is collected in the week following birth. For women recruited as part of pregnancy surveillance, births are identified by routine follow up by field staff, by village-based key informants, or because women self-report their own birth. All infants born in selected labour wards in the study areas are screened for enrolment.

##### Screening and enrolment

After the birth of a live infant, parents are asked for consent to participate in the study. Those who give written informed consent are screened to determine if the infant meets the eligibility criteria. Those consenting and eligible are given a single dose of 50,000 IU of vitamin A or placebo. The number written on the blister pack of vitamin A or placebo becomes the infant's ID, and an identity card is issued.

Infants are randomized individually within the geographical strata according to a computer-generated random number list, arranged in blocks of 20, in which unique identification numbers corresponds to one of the two interventions. Each new infant is assigned the next available study number. Previous experience has demonstrated feasibility to conduct the individually randomized controlled trial in these study clinics and communities.

##### Monitoring of potential adverse events

Trained FWs visit enrolled infants at home one day and three days after dosing to monitor possible side effects of vitamin A supplementation. A standard form is completed documenting symptoms of potential side effects. For each infant, reported symptoms including bulging fontanelle, diarrhoea, vomiting, fever, inability to suck or feed, and convulsions are recorded. In addition, caregivers of newborns are asked if they notice any unexpected clinical signs or behaviour changes in the baby since the time of supplementation. If a problem is reported, study staff refers the family to the nearest health facility, where any morbidity is managed per the standard of care established by the Ministry of Health in Tanzania.

##### Follow up during infancy

Field staff visit the home of enrolled infants at 1 month, 3 months, 6 months, and 12 months after birth. The main purpose of the visits is to ascertain survival status during infancy. Additionally, information about symptoms of illness in the past month (cough, refusal to eat, fever, difficulty breathing, chest retraction, convulsions, vomiting, and diarrhoea) and any past morbidity that resulted in hospitalization are collected. For hospitalizations, detailed information is sought from medical records or mother's report about the date of admission, length of hospital stay, and the reason for admission.

During the visits, FWs assess if the child is alive and still a resident in the study area. Key informants within the demographic surveillance areas also ascertain vital status and report it to the study team. In case of a death of a study child, the event is documented, and trained field staff completes a verbal autopsy with the child's primary caregiver. For women who travel out of study area, attempts to maintain contact with her through cell phone or relatives in the area are made in order to collect information on the child's vital status.

##### Blood sample

A blood sample is requested from 728 infants at 2 weeks of age, and samples are also requested from 728 mother-infant pairs at 3 months postpartum. The samples are collected over the course of one year to cover all seasons, and specific geographical zones are sampled on a rotating basis in order to facilitate logistics. Thus, every week 14 infants that meet the age requirements and live within the designated geographical area are randomly selected. Samples are centrifuged, and serum aliquots are frozen until testing of samples.

##### Data management

Data are captured electronically using touch screen tablet PCs and net books. Software for real-time data entry has detailed range and consistency checks to ensure data quality. Data are uploaded to the main server in Dar es Salaam via the cell network or wireless internet where possible. Data are further reviewed by data management team, and identified discrepancies are resolved by site supervisors or the field coordinator. Data are uploaded each month to WHO.

### Standardization and quality assurance of the three studies

#### Data collection instruments

Across the three studies, there are shared questionnaires that each contains a set of "core" variables collected by interview, examination, anthropometry or laboratory analyses. Each core variable has a standard definition, acceptable range limits, and is maintained in agreed upon data formats.

#### Training and standardization

Research staff of all three studies has been carefully trained to conduct surveillance, interview families, obtain informed consent, administer the intervention/placebo capsules, collect baseline and follow up information and in electronic data capture (India and Tanzania).

#### Supervision and quality checks

To ensure quality of data, spot checks are done for each FW at least once a month to confirm whether the workers are visiting families. Workers who have conducted a home visit in the last 6 days are selected and families are called or visited to confirm whether the worker had visited them.

Additionally supervised visits are conducted for each worker once a month to assess and improve the quality of activities done by the worker. Different activities (consenting, screening, capsule administration, post dosing and follow up visits) conducted by workers are observed by supervisors by accompanying FWs on these visits. Each worker is accompanied at least once a month. During supervised visits the following aspects are evaluated; worker appearance and quality of interaction with the family, whether the questions in the form are asked correctly and procedures, if relevant (e.g. weighing and capsule administration), are performed correctly.

#### Site monitoring

WHO technical staff conducts at least two monitoring visits to each site every year. A detailed structured review of study implementation is done at each visit. The monitors make direct observations of study implementation and data management activities. The key areas that are monitored include the pace of recruitment, consent procedures, storage and use of study supplements, follow up visits, data collection, collection transport and storage of blood samples and data management. The recommendations arising from the site visit are discussed for implementation with the Principal Investigators.

#### Data monitoring

Data range and consistency checks are built into the data entry system and any discrepancies are returned to the field for verification. Data from all studies are sent every month to a central data repository which is established at WHO. Data quality checks are applied on a monthly basis and feedback provided to the study sites.

#### Capsule testing

The vitamin A capsule supplier provided evidence of rigorous stability testing and the certificates of analysis. Additionally an independent laboratory checks to confirm the content of the capsules throughout the study. Every three months, twenty randomly selected unused backup capsules are selected from among those capsule strips used for enrolments in the previous three months and sent to an independent laboratory for analysis of vitamin A content (VITAS, Norway).

#### Laboratory standardization

Blood samples are collected, transported and analysed according to a quality control/assurance protocol to assure retinol contents within accepted ranges. Laboratories performing analysis of blood samples for vitamin A concentrations participated in the VITAL-EQA program from the US Centers for Disease Control and Prevention (CDC) for quality control.

### Analysis plan for the three studies

#### Definitions

The primary outcome of the study is defined as a death between supplementation and 180 days of life (6 months). Secondary mortality outcomes are defined as a death between supplementation and 28 days of life, and a death between supplementation and 365 days of life. Severe morbidity is defined as one or more hospitalizations due to any illness between supplementation and day 180 of life. A hospitalization is defined as an admission to hospital as an inpatient, as reported by the mother. Infants will only contribute one hospitalization episode to the analysis, regardless of how many times they were hospitalized in the first six months of life.

Potential adverse events are defined as specific events occurring within 3 days of supplementation. These events include all deaths within 3 days of supplementation; bulging fontanelle confirmed by the research team through a physical examination of the infant; or primary caregiver reports of fever, vomiting, diarrhoea, inability to suck or feed, or convulsions in the first 3 days post supplementation.

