### Objectives of each trial

The primary objective of these studies is:

■ To determine if vitamin A supplementation (50,000 IU) given to neonates once orally either on the day of birth or in the next 2 days will reduce mortality in the period from supplementation to 6 months of age by at least 15% as compared to placebo.

The secondary objectives of the studies are:

■ To determine if vitamin A supplementation (50,000 IU) given to neonates once orally either on the day of birth or in the next 2 days will reduce mortality in the period from supplementation to 12 months of age.

■ To determine the efficacy of vitamin A supplementation (50,000 IU) given to neonates once orally either on the day of birth or in the next 2 days in reducing mortality in the period from supplementation to 28 days of age.

■ To determine the efficacy of the above intervention in reducing the incidence of severe morbidity defined as hospitalizations due to any illness in the period from supplementation to 6 months of age.

■ To document the potential adverse effects of vitamin A such as bulging fontanelle, vomiting, irritability, fever, diarrhoea, inability to suck or feed, convulsions or any other condition that caused parents to be concerned, in the 3 day period following administration of the supplement.

■ To determine the vitamin A status of a subsample of infants at 2 weeks and 3 months of age in the vitamin A supplementation and placebo groups.

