### Overview of Study Design

The studies are individually randomized, double-masked, placebo controlled trials. The study participants are neonates who are likely to stay in the study areas until at least 6 months of age, who are able to feed orally at the time of enrolment and whose parents provide written informed consent for study participation. Neonates randomized to the intervention group receive 50,000 IU vitamin A on the day of birth or in the next two days, and those randomized to the control group receive placebo. Potential adverse events are determined during visits by a study worker one day and three days after supplementation. A potential adverse event is defined as any harmful and/or undesired effect as reported by the family which may have resulted from the use of the vitamin A supplement. These include presence of bulging fontanelle, vomiting, fever, diarrhoea, inability to suck or feed, and convulsions. Mortality and morbidity information are collected through periodic home visits by a study worker during infancy (Figure 1).

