#### Adverse events

Adverse events in the vitamin A and placebo groups will be tabulated [29]. The denominator will be all enrolled infants. The absolute risk of an adverse event per arm and per adverse event type will be presented.

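### The analysis definition of potential adverse events leaves out two items of the safety objective and counts bulging fontanelle only when staff confirm it

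*Protocol article*

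**What the plan says.** The article describes the 3-day safety outcome in several places.

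- **Objectives of each trial** sets a secondary objective to document possible adverse effects in the 3 days after dosing, "such as bulging fontanelle, vomiting, irritability, fever, diarrhoea, inability to suck or feed, convulsions or any other condition that caused parents to be concerned".
- **Overview of Study Design** defines a potential adverse event as any harmful or undesired effect "as reported by the family which may have resulted from the use of the vitamin A supplement". Bulging fontanelle is among its examples. Visits are planned one day and three days after dosing.
- **Tanzania, Monitoring of potential adverse events**: "reported symptoms including bulging fontanelle, diarrhoea, vomiting, fever, inability to suck or feed, and convulsions are recorded". Caregivers are also asked an open question about unexpected signs or behaviour since dosing.
- **Ghana, Monitoring of potential adverse events** asks caregivers to tell the team about unexpected signs within three days, in addition to the two visits. The corresponding India section describes the two visits only.
- **Definitions**, in the analysis plan, limits potential adverse events to specific events within 3 days. These are deaths; "bulging fontanelle confirmed by the research team through a physical examination of the infant"; and "primary caregiver reports of fever, vomiting, diarrhoea, inability to suck or feed, or convulsions in the first 3 days post supplementation".
- **Adverse events**, in the analysis plan, takes all enrolled infants as denominator: "The absolute risk of an adverse event per arm and per adverse event type will be presented".

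**The concern.** The definition that feeds the table is narrower than the objective it serves, in two ways. Irritability and the open category of parental concern appear in the objective but not in the list of events to be counted. Bulging fontanelle is a family-reported sign where the outcome is described and collected, yet it needs a staff examination before it is counted.

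The objective is to document possible harm, and the planned summary is an absolute risk per arm. If the definition is applied literally, part of that objective goes unreported. For bulging fontanelle, the reported risk then depends partly on whether the sign was still present when someone from the study examined the infant. The results are meant to inform global policy on giving this supplement to newborns, so the safety table should cover what the objective promised.

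**Working it through.** The article states no adverse event rate, so there is no figure to reproduce. The check is a comparison of the sections, followed by an illustration of why the effect on bulging fontanelle cannot be sized.

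**Step 1. Event types, side by side**

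| Event | Objectives | Overview | Tanzania monitoring | Definitions (analysis) |
|---|---|---|---|---|
| Fever, vomiting, diarrhoea, feeding problem, convulsions | Yes | Yes, family report | Yes, reported | Yes, caregiver report |
| Bulging fontanelle | Yes | Yes, family report | Yes, reported | Only if confirmed by examination |
| Irritability | Yes | Not named | Not named | Absent |
| Any other parental concern | Yes | Covered by the general wording | Covered by the open question | Absent |
| Death within 3 days | Not named | Not named | Not named | Yes |

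Two types in the objective have no place in the counted list, and one type changes its basis of ascertainment.

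**Step 2. What this does to the table**

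Risks are presented by event type. Omitting irritability and the open category leaves those types without a row; it does not lower the risk shown for any other type. Only a combined risk of any adverse event, if one is shown, would be smaller under the narrower list.

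The five symptoms in the first row of the table are counted from caregiver report over the whole 3 days. They need not be present at a visit, so having only two scheduled visits does not by itself lose them.

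Bulging fontanelle differs. With all enrolled infants in the denominator, an infant whose reported bulge was not confirmed stays in the denominator and contributes nothing to the numerator.

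**Step 3. Can the loss be sized?**

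The inputs needed are the distribution of onset, the duration of the sign, and when examinations take place. The article gives only the scheduled visits, on days 1 and 3. Purely as an assumption, let onset be uniform over days 0 to 3, duration be L days, and examinations take place only at exactly day 1 and day 3. For L up to 2 days:

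share of episodes present at an examination = (min(L, 1) + min(L, 2)) / 3

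- L = 0.25 (6 h): (0.25 + 0.25)/3 = 17% seen, 83% not seen
- L = 0.5 (12 h): (0.5 + 0.5)/3 = 33% seen, 67% not seen
- L = 1 (24 h): (1 + 1)/3 = 67% seen, 33% not seen
- L = 1.5 (36 h): (1 + 1.5)/3 = 83% seen, 17% not seen
- L = 2 (48 h): (1 + 2)/3 = 100% seen, none missed

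A simulation of 200,000 draws per duration agreed with the formula. The answer runs from most episodes to none, depending wholly on a duration that the article does not give. It also ignores any examination prompted by a caregiver between visits, which the Ghana arrangement makes possible. The illustration shows that the direction of a loss is plausible for short-lived bulges. It is not an estimate.

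**The case against.** A fair defence has several parts.

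- **The lists may be open.** The objective's list is introduced as illustrative, and the analysis definition says "These events include all deaths within 3 days of supplementation" before going on, so it need not be exhaustive. This stands only in part. The same definition speaks of specific events and reads as a complete list; if it is meant to be open, it should say so.
- **Recording and counting are different steps.** Taking a family report and then requiring confirmation of a physical sign is a coherent sequence, and confirmation removes false positives. This stands, and is the reason to keep a confirmed count. It does not justify showing only that count when the outcome is elsewhere defined by family report.
- **Missed cases need not bias the comparison.** If the same fraction s of true cases is confirmed in both arms and specificity is high, the risks become s × p in each arm and their ratio is unchanged. That is correct, but the plan presents absolute risks, and those are scaled down by s.
- **Detail belongs in the full protocol or SAP.** This would answer a point about missing detail. Here the article itself states an analysis definition, and that definition does not match its own objective.
- **Site differences.** The India section is shorter and may simply be condensed, and each trial is analysed separately, so differences in ascertainment between sites do not bias an arm comparison. This stands.

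A reader might infer that the absolute risks of adverse events in general will be understated. The article does not support that. Reporting is by event type, five of the symptoms rest on caregiver report for all 3 days, and confirmation of bulging fontanelle is not restricted to the scheduled visits.

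**Conclusion.** The mismatch is real and limited. As written, the analysis definition gives irritability and other conditions of parental concern no place in the adverse event table, although the safety objective names both. It also counts bulging fontanelle on a stricter basis than the sections that describe and collect it, so its absolute risk may be understated where a reported bulge resolves before examination. The size of that effect is unknown and could be nil, because onset, duration and unscheduled examinations are not documented. The other five caregiver-reported symptoms are unaffected, as is the mortality analysis; deaths within 3 days are counted and reviewed by the DSMB. The conclusion assumes that the definition would be applied as it reads, as a closed list. The matter concerns a secondary descriptive table, and merits correction while the trials are ongoing and the teams masked.

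**What to change.** Bring the Definitions section into line with the objective, the overview and the Tanzania monitoring section:

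1. Add irritability and other conditions of concern to parents to the tabulated events. Use the information already sought at the day-1 and day-3 contacts, and state for each trial where irritability was not asked about specifically.
2. Show bulging fontanelle in two rows, per arm in each trial: caregiver-reported or found by staff, and confirmed by examination.
3. Say whether the list of events is complete.

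The cost is a change of wording and a few table rows. The downside is that the reported row will include some false positives. With masked arms these should occur at similar rates in both. They would dilute a ratio computed from that row, which is why the confirmed row stays beside it.
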